#### Analyses and Statistical Considerations

To determine whether the NMIBC-SI fulfills fundamental prerequisites for rigorous measurement as defined by established psychometric criteria [32] and the US FDA guidance [11], standard psychometric tests for acceptability, data quality, internal reliability, and factor analysis construct validity will be performed. Table 1, adapted from Gorecki, 2013 [33], presents full details of the tests and criteria used in the psychometric evaluation.

The purpose of the item reduction analysis is to produce a psychometrically robust version of the NMIBC-SI. Standard psychometric tests and criteria, as described in Table 1, will be performed to identify and retain items with strong psychometric properties and eliminate items with poor psychometric properties to produce a shorter, item-reduced version of the NMIBC-SI. These analyses will also evaluate the hypothesized subscales of the NMIBC-SI.

Missing data will not be imputed. The frequency of missing data will be determined, and items with a response rate of <80.0% (180/225) will be investigated.

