#### Sample Size

Approximately 225 patients newly diagnosed with NMIBC will be required to provide sufficient subjects for statistical assessment of test-retest reliability [34,35] and clinical validity in terms of both sensitivity to differences between patient groups [36] and responsiveness to clinically important change [37]. See section on Sample Size for Field Test 1 for sample size justification.

**Table 1 table1:** Psychometric tests and criteria.

Property				Definition/test	Criteria for acceptability	
1. Item analysis				Identify items for possible elimination due to weak psychometric performance; assessed on the basis of (1) exploratory factor analysis with principal axis factoring and (2) item- and scale-level analyses	Exploratory factor analysis: items with a factor-loading coefficient ≥0.4 will be retained in each subscale. Applied to all items: (1) missing data <5%; (2) maximum endorsement frequencies <80% (ie, the proportion of respondents who endorse each response category), including floor or ceiling effects <80% (ie, response categories with high endorsement rates at the bottom and top ends of the scale, respectively); (3) evidence of item responsiveness as assessed by significant improvement between baseline and test of cure assessments (field test 2 only)	
2. Acceptability				The quality of data; assessed by completeness of data and score distributions	Missing data for summary scores <20%; normal distribution of endorsement frequencies across response categories (ie, absence of skew, endorsement rates between 0.20 and 0.80); and floor or ceiling effects for summary scores <10%	

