#### Analyses and Statistical Considerations

Analyses will evaluate the measurement properties of the final version of the NMIBC-SI, using psychometric tests described for field test 1 (Table 1). Additional tests for reliability (test-retest: correlations for summary scores ≥.70), clinical validity (in terms of sensitivity to groups known to differ clinically and responsiveness to clinically meaningful change over time [37]), and estimation of minimal important difference (interpretability) [39] will be undertaken. Evaluation of subscales will be determined by factor analysis and against external criteria (between-group validity: convergent, discriminant, and known group differences validity). To evaluate convergent and discriminant validity, we will compare NMIBC-SI scales with the scales within the EORTC QLQ-C30 and QLQ-NMIBC24 measures. NMIBC-SI scores for patients by risk and treatment groups will be compared to evaluate known group differences. Risk groups are defined as low, intermediate, and high (see Textbox 1) [6]. Treatment groups are defined as follows: (1) cystoscopy alone or TURBT, (2) course of intravesical chemotherapy, and (3) course of intravesical BCG. We hypothesize that low-risk patients will have lower levels of treatment-related problems at follow-up time points compared with high-risk patients, who have more intensive treatments. Factor analysis, together with the results of other item-level analyses described in Table 1, will be used to investigate hypothesized subscales.

Analyses of the clinical aims will include: (1) evaluation of PRO changes over time, from diagnosis to peak treatment and at 1 year; (2) comparison of PROs between the 3 risk groups at each time point; and (3) head-to-head comparison of the relative discriminatory ability of the NMIBC-SI and the EORTC QLQ-NMIBC24. The pretumor resection assessment (T1) will be at diagnosis and is considered our baseline assessment. Patients are not expected to have any treatment-related problems at this point. The subsequent 3 time points (Table 2) are intended to capture short-term, intermediate, and long-term levels of problems, and each will be compared with baseline (T1).

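### Table 1's acceptability band of 0.20 to 0.80, read per response category as the table defines endorsement, cannot be met with six or more categories and fails typical symptom items with four or five

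*Protocol article*

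**What the plan says.** All of this is in the protocol article. Table 1 lists the psychometric tests and their pass criteria.

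- **Row 1 (Item analysis)** serves to "Identify items for possible elimination due to weak psychometric performance". Its distribution rule is an upper limit only: "maximum endorsement frequencies <80% (ie, the proportion of respondents who endorse each response category". Floor and ceiling effects carry the same 80% limit.
- **Row 2 (Acceptability)** is described as "The quality of data; assessed by completeness of data and score distributions". Its criteria include "normal distribution of endorsement frequencies across response categories (ie, absence of skew, endorsement rates between 0.20 and 0.80", alongside limits on missing data and on floor or ceiling effects for summary scores.
- **Field Test 1, Analyses and Statistical Considerations**, gives the table its role in item reduction: "Standard psychometric tests and criteria, as described in Table 1, will be performed to identify and retain items with strong psychometric properties".
- **Field Test 2, Analyses and Statistical Considerations**, applies the same Table 1 tests to the final version. Of the pre-resection assessment (T1) it says: "Patients are not expected to have any treatment-related problems at this point".

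The number of NMIBC-SI response options is not given. Pretesting is said to have explored them, and only the two EORTC comparators are described, as rated 1 to 4.

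**The concern.** Row 2 asks for two things that do not fit together on most graded scales. A bell shape has thin ends, whereas a floor of 20% in every category forces a nearly flat distribution once there are four or more categories. Symptom and side-effect items usually pile up at the no-problem end, and the article expects this at T1 for treatment-related problems. Such an item can satisfy row 1 and still fail row 2.

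At stake is how the index is shortened and then judged. If row 2 is applied as printed, it can flag items for the shape that symptom data normally take rather than for weak measurement. If analysts instead decide what the band means once they have seen the distributions, the criterion is no longer prespecified.

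**Working it through.** **Inputs.** Band 0.20 to 0.80 (Table 1, row 2). Endorsement as the share choosing each category (row 1). Upper limit of 80% in any category (row 1). About 225 patients per field test (Sample Size sections). The number of categories k is not stated, so a range is shown. The band is a stated criterion, so there is no derived figure to reproduce.

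**Step 1: can the band be met?** The k shares sum to 1. All shares at or above 0.20 requires 0.20 × k ≤ 1, and the largest share any category can then hold is 1 − 0.20 × (k − 1).

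| k | Minimum total, 0.20 × k | Largest permitted share |
|---|---|---|
| 2 | 0.40 | 0.80 |
| 3 | 0.60 | 0.60 |
| 4 | 0.80 | 0.40 |
| 5 | 1.00 | 0.20 (all equal) |
| 6 or more | 1.20 or more | impossible |

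The printed upper bound of 0.80 can therefore be reached only with two categories.

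**Step 2: does a normal distribution meet it?** Take a centred normal cut at equally spaced points w SD apart, with Φ the standard normal distribution function.

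- k = 3, cuts at ±w/2. The end shares are 1 − Φ(w/2) and the middle share is 2Φ(w/2) − 1. All reach 0.20 for w from about 0.51 to 1.68.
- k = 4, cuts at −w, 0, w. The end shares are 1 − Φ(w) and the inner shares Φ(w) − 0.5. All reach 0.20 for w from about 0.53 to 0.84. At w = 0.75 the shares are 22.7/27.3/27.3/22.7% (pass); at w = 1 they are 15.9/34.1/34.1/15.9% (fail).
- k = 5. No spacing between 0.01 and 3 SD passes. At w = 1 the shares are 6.7/24.2/38.3/24.2/6.7%.

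**Step 3: illustrative symptom shapes at k = 4.** These are assumed distributions, not trial data.

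| Shares (%) | Row 1 (<80%) | Row 2 (each 20 to 80%) |
|---|---|---|
| 60/25/10/5 | pass | fail |
| 50/25/15/10 | pass | fail |
| 40/30/20/10 | pass | fail |
| 40/20/20/20 | pass | pass, at the boundary |

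**Step 4: sampling variation at n = 225.** The floor is 0.20 × 225 = 45 respondents in each category.

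- k = 5, truly 20% in each: 5 × 45 = 225, so only exactly 45 in every category passes. The probability is 225!/(45!)^5 × 0.2^225, about 0.00003.
- k = 4, by multinomial simulation (200,000 draws): a truly flat 25/25/25/25% item passes with probability 0.87, and a true 22/28/28/22% item with probability 0.59.

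**The case against.** **The band may not be meant per category.** Row 2 speaks of endorsement rates without repeating row 1's explanation, and the table is adapted from an earlier source that is not at hand. The band could have been meant for the proportion endorsing an item at all. That is possible, but the printed sentence ties it to response categories, and row 1 explains endorsement as a share of each category. The article does not state the other meaning.

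**The rows have different purposes.** Row 1 screens items and row 2 describes data quality, and their limits differ elsewhere too: missing data under 5% against under 20%, floor or ceiling effects under 80% against under 10%. A stricter rule in another row is not in itself a contradiction. This stands, so the mismatch with row 1 only supports the point. The difficulty inside row 2 remains: response categories belong to items, so this clause cannot be about summary scores alone.

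**T1 is weak evidence for field test 1.** The expectation at T1 concerns treatment-related problems before resection in field test 2. Item reduction uses field test 1 patients, recruited around active treatment, when symptoms are likelier. This also stands. The T1 statement bears on field test 2 only.

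**Stronger readings that the document does not support.** A reader might infer that the rule fails almost every item whatever its quality, or that a normal distribution always fails with four categories. Neither follows: k is unknown, scales with two or three categories can pass, and four-category normals with narrow spacing pass. A reader might also infer that failing row 2 removes an item. The article speaks of possible elimination, judged on several criteria together, including factor loading and missing data.

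**Conclusion.** The criterion is misstated and should be corrected before it is applied. On the article's own explanation of endorsement, it is impossible with six or more categories, attainable with five only by an exactly equal split, and with four it caps every category at 40%, which excludes the usual right-skewed symptom shapes that row 1 accepts. With two or three categories it can be met.

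The size is conditional on the number of NMIBC-SI response options, which is not stated. The four-option case is plausible because the comparators use it, but that is an assumption. The consequence is a risk that sound items are flagged, or that the rule is reinterpreted after the data are seen; it is not a demonstrated loss of items. The conclusion rests on the per-category reading, which is the one the text supports.

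**What to change.** In Table 1, row 2:

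1. Stop applying the 0.20 lower bound to each response category.
2. Keep row 1's limit (no single category at or above 80%) as the item-level distribution criterion.
3. If a 0.20 to 0.80 band is wanted, define it as the proportion reporting any problem on the item.
4. Report skew and the full category distribution descriptively, without pass or fail.

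On point 3, the choice should be deliberate. If the lowest category means no problem, requiring at least 20% with any problem is the same as allowing at most 80% in that category, which nearly repeats row 1. What the band would add is its upper end: the 15.9/34.1/34.1/15.9% item has 34.1 + 34.1 + 15.9 = 84.1% reporting a problem and would be flagged as too widely endorsed.

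The cost is a rewording of one table cell, with no new data. The downside is that one pass/fail criterion becomes descriptive.

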**3. Reliability**						
	3.1 Internal consistency			The extent to which items comprising a scale measure the same construct (eg, homogeneity of the scale); assessed by Cronbach alpha and item-total correlations	Cronbach alpha for summary scores ≥.70 and item-total correlations ≥.30	
	3.2 Test-retest reliability (field test 2 only)			The stability of a measuring instrument; assessed by administering the instrument to respondents on two different occasions and examining the correlation between test and retest scores	Test-retest reliability and intraclass correlations for summary scores ≥.70	
**4. Validity**						
	4.1 Content validity			The extent to which the content of a scale is representative of the conceptual domain it is intended to cover; assessed qualitatively during the questionnaire development stage through pretesting with patients, expert opinion, and literature review	Qualitative evidence from patients, expert opinion, and literature review that items in the scale are representative of the construct being measured	
	**4.2 Construct validity**					
		Within-scale analyses		Evidence that a single entity (construct) is being measured and that items can be combined to form a summary score	Confirmatory factor analysis: (1) items with a factor-loading coefficient ≥0.4 and (2) moderate to high correlations between scale scores	
		**Analyses against external criteria**				
			Convergent validity	Evidence that the scale is correlated with other measures of the same or similar constructs; assessed on the basis of correlations between the measure and other similar measures	Correlations are expected to vary according to the degree of similarity between the constructs that are being measured by each instrument. Specific hypotheses are formulated and predictions tested on the basis of correlations	
			Discriminant validity	Evidence that the scale is not correlated with measures of different constructs; assessed on the basis of correlations with measures of different constructs	Low correlations between the instrument and measures of different constructs	
			Known groups differences	The ability of a scale to differentiate known groups; assessed by comparing scores for subgroups that are expected to differ on the construct being measured	Significant differences between known groups or difference of expected magnitude	
5. Responsiveness				The ability of a scale to detect clinically significant change following treatment of known efficacy; assessed by examining within-person change scores before and after treatment and calculating an effect size statistic (mean change score divided by standard deviation of pretreatment scores)	Moderate to large effect sizes (small 0.2, moderate 0.5, and large 0.8 or higher)	

**Table 2 table2:** Patient-reported outcome assessment schedule.

Risk group	Assessed within 3 months before tumor resection	Assessed within 4 to 10 days after the tumor resection	Assessed within 1 month after the end of induction intravesical therapy^a^	Assessed within 1 month before the 1-year cystoscopy (or at early cessation due to adverse events^b^)
High	T1	T2	T3	T4
Intermediate	T1	T2	T3	T4
Low	T1	T2	T3^c^	T4
~n	225	225	225	225

^a^A minimum of 25 participants from each risk group will be asked to complete an additional questionnaire pack 3 to 7 days after T3.

^b^Preferably before cystoscopy.

^c^For the low-risk group, T3 will be 8 weeks after resection.

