**Methods:**

The NMIBC-SI will be evaluated in 2 field tests across a total of 3 years. Field test 1 is a cross-sectional study design involving 225 adult NMIBC patients recruited while undergoing active treatment or those who completed final treatment within the past week. Data collected include patient demographics, clinical features of the tumor, risk category, treatment type, comorbidity, and PROs. Field test 2 is a prospective longitudinal study involving 225 newly diagnosed NMIBC-SI patients. Clinical data and patient-completed questionnaires will be collected at 4 time points during treatment: before tumor resection, 1 week after resection, end-of-induction intravesical therapy, and 1-year follow-up. Standard psychometric tests will be performed to assess the reliability, validity, responsiveness, and clinical utility of the NMIBC-SI.

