Guidelines for the management of NMIBC are based on evidence for the effectiveness of treatments in reducing risk of bladder cancer progression and recurrence. Evidence for reductions in health-related quality of life (HRQoL) and associated side effects with each treatment are not incorporated into the decision-making process because they have been poorly documented (see section below on Critical Gaps in Knowledge About HRQoL and Patient-Reported Outcomes [PROs] in NMIBC). This is despite the fact that these treatments can cause substantial side effects and local and systemic toxicity. For example, the commonly used BCG has proved effective in reducing recurrences in patients with high-grade tumors and carcinoma in situ, but it can cause moderate to severe local and systemic side effects, and only 16% are able to complete their full treatment schedule [10].

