#### Clinical Aims (Field Test 2)

To assess and compare key PROs across the full range of contemporary treatments for NMIBC and over-the-disease trajectory, including acute treatment and 1-year survivorship.To compare PROs between patients with low-, intermediate-, and high-risk NMIBC.

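### Table 2 lets the single label T4 mean either the 1-year assessment or an assessment at early cessation for adverse events, yet T4 is analysed as the 1-year, long-term result

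*Protocol article*

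**What the plan says.** The last column of Table 2 (Patient-reported outcome assessment schedule, field test 2) gives T4 two timings under one label: "Assessed within 1 month before the 1-year cystoscopy (or at early cessation due to adverse events". A footnote attached to the second timing adds that the form should preferably precede cystoscopy. The table has no separate column for an early-cessation form, and its bottom row shows about 225 patients at every time point.

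Elsewhere T4 is a single fixed time:

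- The abstract (Methods) lists the last two assessments as "end-of-induction intravesical therapy, and 1-year follow-up".
- Clinical Aims (Field Test 2) describes the disease trajectory as "including acute treatment and 1-year survivorship", so the 1-year state is set apart from acute treatment.
- Analyses and Statistical Considerations for field test 2 says "The subsequent 3 time points (Table 2) are intended to capture short-term, intermediate, and long-term levels of problems", and compares each with T1. It also plans "evaluation of PRO changes over time, from diagnosis to peak treatment and at 1 year" and "comparison of PROs between the 3 risk groups at each time point".

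No passage separates the two kinds of T4, or says whether a patient who ceases early also completes a form at 1 year.

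**The concern.** A score collected because adverse events led to cessation describes the patient around that event. A score collected near the 1-year cystoscopy describes the longer-term state. Averaged under one label, they give a mean that belongs to no single time.

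This is potential bias and not only noise, for two reasons. First, the trigger is closely tied to the outcome: bad symptoms bring T4 forward. Second, the trigger probably differs by group. The Introduction describes low-risk care as cystoscopies, possible resections and single instillations, and high-risk care as a 6-week BCG induction followed by 1 to 3 years of maintenance. It also says that BCG can cause moderate to severe side effects. Early scores should therefore fall mainly in the groups on continuing intravesical therapy.

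That is the direction of the study's own known-groups hypothesis: "We hypothesize that low-risk patients will have lower levels of treatment-related problems at follow-up time points compared with high-risk patients". A risk-group difference at T4 could then owe something to when the form was completed. The change from T1 to T4 would be blurred as well, and a patient who stopped during induction could have T3 and T4 close together.

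The rule governs data collection. If no 1-year form is collected from these patients, later analysis cannot fully repair the loss.

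**Working it through.** The plan states no figure for this bias, so there is none to reproduce. The check asks how large it could be under stated assumptions.

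**Inputs from the protocol article**

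- Field test 2 has about 225 patients in three risk groups. The 225 agrees with the subjects-per-item rule to which the plan refers: 5 × 30 = 150, 10 × 30 = 300, midpoint 225.
- Table 1 takes 0.2, 0.5 and 0.8 SD as small, moderate and large effects.
- On BCG completion, the Introduction says "only 16% are able to complete their full treatment schedule". Neither reasons nor timing are given.

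**Assumptions (not in the document)**

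- Equal groups: 225 / 3 = 75 each. The plan asks only for adequate representation.
- f = share of the high-risk group whose T4 is taken at cessation; f = 0 in the low-risk group.
- d = excess of the cessation score over the same patients' 1-year level, in SD; range 0.5 to 1.0.
- No true difference at 1 year, SD 1 within each component, two-sided 5% normal test.

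**Formulas**

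- Bias in the group's T4 mean = f × d.
- Variance of the mixed group = 1 + f(1 − f)d².
- SE of the difference = √[(1 + 1 + f(1 − f)d²) / 75].
- Chance of a significant result = Φ(bias/SE − 1.96) + Φ(−bias/SE − 1.96).

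**One case in full:** f = 0.20, d = 1.0. Bias = 0.20 SD. Variance = 1 + 0.20 × 0.80 × 1 = 1.16. SE = √(2.16/75) = 0.170. Bias/SE = 1.18. Chance of significance = Φ(−0.78) + Φ(−3.14) ≈ 0.22.

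| f | Bias, d = 0.5 to 1.0 (SD) | Chance of a significant high-versus-low difference when the true 1-year difference is zero |
|---|---|---|
| 0.05 | 0.03 to 0.05 | 5 to 6% |
| 0.10 | 0.05 to 0.10 | 6 to 9% |
| 0.20 | 0.10 to 0.20 | 9 to 22% |
| 0.30 | 0.15 to 0.30 | 15 to 42% |

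For scale, 75 versus 75 gives 80% power for (1.96 + 0.84) × √(2/75) ≈ 0.46 SD. A bias of 0.30 SD is about two thirds of that; 0.03 SD does not matter.

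The 16% completion figure does not supply f. Its complement, 84%, covers non-completion for any reason on schedules that the Introduction puts at up to 3 years. It is at most an upper bound on cessation for adverse events before the 1-year visit.

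**The case against.** The strongest reply is that Table 2 is ambiguous and not plainly wrong. It does not say whether treatment or study participation ceases, or whether a 1-year form is still sent. If it means leaving the study, a form on exit recovers data that would otherwise be lost. This stands as a limit on certainty. It does not remove the problem, because the exit form would still carry the T4 label and enter the 1-year comparisons.

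Several stronger readings are tempting, and the document does not support them:

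- *No 1-year data will exist for patients who cease early.* The table's wording makes this likely for T4 but does not state it.
- *The early form is taken at peak toxicity.* No passage places it there, and the footnote on cystoscopy suggests some freedom in timing.
- *Low-risk patients can never trigger it.* That follows only if cessation means stopping a continuing course of treatment.
- *The known-groups difference is inflated by construction.* It is inflated only to the extent that early cessation occurs. A patient stopping for adverse events has real symptoms, and a high score is correct measurement at that moment; the fault lies in calling it a 1-year score. The hypothesis also covers T2 and T3, which the rule leaves alone, and the two bladder-specific instruments are completed in the same pack, which largely protects the head-to-head comparison.

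Two further points stand. High-risk patients who continue may still be on maintenance at 1 year, so risk group and time since treatment are partly confounded whatever is done with T4. And the handling of flagged early forms can be left to an analysis plan that is not shown; the definition of the visit, and whether a 1-year form is collected, cannot.

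**Conclusion.** The concern holds as a defect in the definition of T4. One label has two timings, the analyses treat it as one, and nothing in the article reconciles them. Read naturally, the rule is outcome-dependent, probably falls unevenly across risk groups, and favours the study's own hypothesis.

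Its size is unknown. It depends wholly on f and d, which the document does not give, so the tabulated range from negligible to 0.30 SD shows what could happen and is not an estimate. The results exposed are the 1-year clinical aim, the T1 to T4 change and the risk-group comparison at T4. The evaluation of the instrument as a whole is not undermined.

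**What to change.** Reword the T4 column of Table 2 so that T4 is the 1-year assessment for every patient still in the study, including those who stopped treatment early. Make the early-cessation questionnaire an additional assessment with its own label, and say whether cessation refers to treatment or to the study. Leave that form out of the 1-year means, the T1 to T4 change and the T4 risk-group comparisons; it may be analysed on its own, for example for responsiveness. Where the 1-year form is not returned, count T4 as missing and do not substitute the cessation form.

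The cost is one extra questionnaire pack, up to 20 minutes by the plan's own estimate, for patients who stop early, plus a changed table header. Some of these patients will not return the 1-year form, so the loss becomes visible missing data. No treatment rule needs to change. The fix removes the mixing of timings; it does not remove the difference between risk groups in who is still on treatment at 1 year.
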